### Statistical methods

All survey data will be exported from REDCap (Research Electronic Data Capture) [18] to a SAS database for analyses. Data analysts will be blinded to allocation. Descriptive data will be provided for all measures. The frequency (%) of categorical factors will be compared using either the Chi-Square or Fisher’s exact test and t-tests for continuous outcomes such as LDL-C levels. The primary groups analyzed will be the randomized treatment groups – CRS and GRS. We will also conduct supplementary analyses comparing 3 groups: CRS, high GRS, and average/low GRS.

The use of validated, standard measures for many of the behavioral and psychosocial measures will enable comparison of the data with other studies. Within-participant analyses (using each participant as his/her own control) will be performed to evaluate changes in these measures over time. Difference in scores will be examined for the outcomes by comparing post-results assessments to baseline assessments. Logistic regression will be used for binary outcomes (e.g., % achieve accurate understanding of their CHD risk) to compare the change by arm with odds ratios and their associated 95 % confidence intervals. Adjusted comparisons of binary and continuous outcomes will be performed using regression models. All secondary analyses will be based on two-sided tests at a significance level of 0.05. We will conduct subgroup analyses to assess interactions between the intervention and: a) sex and b) family history of CHD.

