**Fig. 1 Fig1:**
[figure not shown]
Flow Diagram of the Proposed Clinical Trial. A flow diagram illustrating the design of the MI-GENES study. A total of 2026 individuals from the Mayo BioBank met the eligibility criteria. Among those 2026, a random sample of 1000 individuals was sent for screening genotyping. A total of 968 individuals had valid screening genotyping results. Recruitment was based on screening genotyping results in order to achieve the targeted enrollment goals of ~110 individuals with high GRS (≥1.1) and ~110 with average/low GRS (<1.1) with the expectation that approximately 10-20 study participants are likely to withdraw from the study or be lost to follow-up

However, whether disclosing results of genetic testing for CHD risk influences relevant clinical outcomes is unknown. We describe the design of a randomized trial to investigate whether disclosing a GRS for CHD, based on genotypes of multiple CHD susceptibility SNPs, leads to lowering of low-density lipoprotein cholesterol (LDL-C) levels. The GRS will be incorporated into the CHD risk estimated based on a conventional risk score (CRS) [7]. We will assess whether disclosure of genetic risk for CHD affects LDL-C levels, initiation of statin therapy, changes in dietary fat intake, physical activity levels and psychosocial measures. We will test the following hypotheses: 1) in patients randomized to receive GRS, LDL-C levels at 6 months will be lower than in participants randomized to receive CRS alone; 2) participants with a ‘high’ GRS will have lower LDL-C levels at 6 months than participants in the average/low GRS category and those randomized to receive CRS alone.

A major challenge to implementing genomic medicine is integration of genomic information into the electronic health record (EHR) [8]. As part of this clinical trial, the genetic testing results will be placed in the EHR. Furthermore, we will disclose CHD risk using a decision aid integrated within the EHR to facilitate shared decision making regarding need for statin therapy [9,10]. This decision aid has been modified to include genetic risk information.

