### Outcomes

The primary outcome will be the change in LDL-C levels between visit 1 and visit 4. We will also assess whether changes in the LDL-C levels at three months following disclosure of CHD risk. We chose change in LDL-C as the primary outcome because there is a well-established causal association of LDL-C with CHD, both lifestyle changes and drug therapy can modify LDL-C levels, and reduction of LDL-C is a major therapeutic goal in both primary and secondary prevention of CHD. Behaviors related to cardiovascular health, including dietary fat intake and physical activity levels will be assessed at baseline and subsequent study visits to examine any changes over time as a result of receipt of CHD risk information. We will assess several psychosocial measures listed in Table 2. The use of validated measures and selection of instruments previously reported in the genetic literature will enable comparison of the current findings with existing literature [12].

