### Sample size and power

In general, studies have confirmed a 5 to 15 % decrease in LDL-C with diet and lifestyle changes and a 30 to 40 % decrease in LDL-C with statin therapy [13,14]. We aimed to detect an LDL-C change of 10 mg/dL to test the first hypothesis that patients randomized to receive GRS would have lower LDL-C levels than patients randomized to CRS alone. For the second hypothesis which will test whether high GRS participants would have lower LDL-C levels that those with low/average GRS and those randomized to receive CRS alone, we aimed to detect an LDL-C change of 15 mg/dL. We assumed the standard deviation of LDL-C change in the entire group to be 25 mg/dL. Under this assumption, the detectable 2-group difference for this change (with 80 % power and 5 % Type I error rate) [hypothesis 1] is 25*sqrt(2/100)*2.8 = 9.9 mg/dL. For hypothesis 2, the detectable decreases in high GRS versus average/low GRS and high GRS versus CRS (with 80 % power and 5 % Type I error rate) are 25*sqrt(2/50)*2.8 = 14 mg/dL and 25*sqrt(1/50 + 1/100)*2.8 = 12.1 mg/dL. Thus, the trial is well-powered to identify an effect of genetic testing that is in the same range as that of diet and exercise.

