### Randomization

The second study visit will be scheduled 6-10 weeks after the initial visit to allow for completion of genotyping and calculation of GRS. One of the study staff will allocate patients (1:1) to the two arms, one group receiving genetically informed 10-year CHD risk (GRS) and the other conventional risk factor information alone (CRS). Randomization will be performed by means of a computer-generated random sequence with stratification for age, gender, and positive family history for CHD using the method previously described by Pocock and Simon [15].

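### The t-test named for LDL-C is valid for the primary change outcome but less efficient than a baseline-adjusted model, and its wording (levels) does not match that outcome (change)

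*Protocol article*

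**What the plan says.** The Outcomes section is explicit: "The primary outcome will be the change in LDL-C levels between visit 1 and visit 4". The Discussion repeats that the primary outcome is change. Sample size and power is on the same scale: "We assumed the standard deviation of LDL-C change in the entire group to be 25 mg/dL". With 100 participants per arm, this gives a detectable difference of 9.9 mg/dL against a target of 10 mg/dL.

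Two other places use LDL-C level instead. Hypothesis 1 in the Background reads "in patients randomized to receive GRS, LDL-C levels at 6 months will be lower than in participants randomized to receive CRS alone". Statistical methods lists "t-tests for continuous outcomes such as LDL-C levels", and this is the only test that the article ties to LDL-C.

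Statistical methods also states: "Adjusted comparisons of binary and continuous outcomes will be performed using regression models". It names no covariates and does not say whether these comparisons are primary or supportive. The Randomization section specifies "stratification for age, gender, and positive family history for CHD using the method previously described by Pocock and Simon". LDL-C is not among the allocation factors.

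**The concern.** An unadjusted t-test does not make full use of data that the trial already collects. Visit 1 LDL-C should predict Visit 4 LDL-C. Age, sex and family history were judged important enough to control allocation, yet nothing ties any of them to the LDL-C comparison.

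The wording adds a second problem. A t-test of 6-month level and a t-test of change estimate the same arm difference under randomization, but with different variances, and the power calculation covers only change. There is little room for lost precision: 99 per arm are needed for 80% power at 10 mg/dL, and about 100 per arm are expected after dropout.

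**Working it through.** **Inputs from the article.** SD of change 25 mg/dL, target difference 10 mg/dL, 80% power, 5% type I error, multiplier 2.8 (Sample size and power); at least 200 participants at the end, so about 100 per arm (Recruitment and baseline characteristics; 1:1 allocation in Randomization).

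**Assumed, because the article does not give it.** An SD of LDL-C level of 28-35 mg/dL, equal at Visits 1 and 4. The Visit 1 to Visit 4 correlation r then follows.

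**Step 1: the article's own figure.** 25 × sqrt(2/100) × 2.8 = 9.9 mg/dL, which reproduces. Power at 10 mg/dL with 100 per arm is 80.7% by the normal approximation and 80.4% with the t distribution.

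**Step 2: implied correlation.** With equal variances, SD(change)² = 2 × SD(level)² × (1 − r), so r = 1 − 25²/(2 × SD(level)²).
- SD(level) 28: r = 1 − 625/1568 = 0.60
- SD(level) 35: r = 1 − 625/2450 = 0.74

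**Step 3: residual SD after baseline adjustment.** SD(adjusted) = SD(level) × sqrt(1 − r²) = 25 × sqrt((1 + r)/2).
- r = 0.60: 25 × sqrt(0.80) = 22.4
- r = 0.74: 25 × sqrt(0.87) = 23.4

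The adjusted variance is therefore 80-87% of the change-score variance.

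**Step 4: the three analyses at 100 per arm.** Detectable difference = SD × sqrt(2/100) × 2.8.

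| Analysis | SD (mg/dL) | Detectable difference (mg/dL) | Power at 10 mg/dL |
|---|---|---|---|
| t-test of change | 25 | 9.9 | 81% |
| Baseline-adjusted model | 22.4 to 23.4 | 8.9 to 9.2 | 89% to 86% |
| t-test of 6-month level | 28 to 35 | 11.1 to 13.9 | 71% to 52% |

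**Step 5: how far this depends on the assumption.** With SD of change held at 25, SD(level) = 25/sqrt(2(1 − r)).
- r = 0.4: level SD 22.8, power of the level test 87%
- r = 0.5: level SD 25, power 81%
- r = 0.7: level SD 32.3, power 59%

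The level test falls below 80% only when r exceeds about 0.5.

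The advantage of adjustment over change does not depend on r or on equal variances. With SDs s1 and s4 at the two visits, the change variance minus the adjusted variance is (s1² + s4² − 2·r·s1·s4) − s4²(1 − r²) = (s1 − r·s4)², which is never negative. This is a large-sample result; only the size of the gain depends on the assumption.

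**Step 6: the allocation factors.** Suppose age, sex and family history explain a fraction R² of the variance of change and are balanced by the minimization. The true type I error of an unadjusted test is then about 2 × (1 − Φ(1.96/sqrt(1 − R²))). For assumed R² of 2%, 5% and 10%, this is 4.8%, 4.4% and 3.9%, so the test is mildly conservative.

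**The case against.** The strongest reply is that the endpoint is already fixed. Outcomes, the power section and the Discussion all say change, and the line in Statistical methods can be read as a general pairing of tests with variable types. On that reading the t-test is applied to change, has the stated power and meets the trial's own target. This stands, and it rules out several stronger conclusions that a reader might draw.

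- *That the primary test is underpowered.* This would require the level analysis to be the primary one, which Outcomes contradicts. It would also require r above about 0.5, and the article gives neither r nor the SD of level.
- *That baseline LDL-C is ignored, or chance imbalance left uncorrected.* A change score subtracts baseline in full; with r below 1 it over-corrects. The fair criticism is inefficiency.
- *That omitting the allocation factors endangers the type I error.* The effect goes in the conservative direction and is small.
- *That adjustment is absent from the plan.* Adjusted regressions of continuous outcomes are planned.

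It can also be said that a condensed article may leave covariate lists to a fuller document that is not shown. That is fair, and the missing list is not the point made here. The point is that the one method the article does name for LDL-C is the less efficient choice, is worded on a scale other than that of the primary outcome, and is not ranked against the regressions mentioned after it.

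**Conclusion.** The point holds as an improvement to the analysis and a wording inconsistency. It is not an error in the power calculation: 9.9 mg/dL is right for an unadjusted comparison of change, and that comparison is valid.

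The cost of keeping it is precision. If the SD of level is 28-35 mg/dL and equal at both visits, baseline adjustment saves 13-20% of the variance and raises power at 10 mg/dL from about 81% to 86-89%, before any gain from the allocation factors. The direction of that gain does not rest on the assumed SD; its size does. Equal variances are also uncertain, since participants who start a statin may widen the spread at Visit 4.

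The wording in hypothesis 1 and Statistical methods should be settled because, in the same assumed range, an analyst who took it literally would run a test with 71-52% power.

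**What to change.** - Name one primary analysis: a linear model of Visit 4 LDL-C on arm, Visit 1 LDL-C, age, sex and family history of CHD. Modelling change instead, with Visit 1 LDL-C as a covariate, gives the same arm effect. Report the adjusted difference with its 95% confidence interval.
- Keep the unadjusted t-test of change as a sensitivity analysis.
- Reword hypothesis 1 and the LDL-C phrase in Statistical methods to match the primary outcome, and say that the regression is primary.
- GRS category may be added as a covariate, but nothing in this point requires it.

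The cost is wording only. According to Recruitment and baseline characteristics, lipids, demographic factors and family history are collected at the first visit. No additional participants or measurements are needed, and the existing sample-size calculation can stay as a conservative basis.

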## Methods and design

### Overall study design

To maximize information yield from the study, we performed an initial screening genotyping of 28 CHD susceptibility SNPs that are not associated with blood pressure (BP) or lipid levels, in 1000 individuals from Olmsted County who were participants in the Mayo Clinic BioBank and met the eligibility criteria. We calculated GRS for each individual based on these 28 SNPs and stratified individuals into two CHD genomic risk categories: high (GRS ≥1.1), and average/low (GRS <1.1). We will enroll 110 patients in each of the two categories for the clinical trial (Fig. 1). The study coordinator will invite these patients by phone to participate in the randomized trial. He/she will inform patients about the trial, confirm eligibility, and subsequently obtain written informed consent. Specifically, the study coordinator will describe the limitations of genetic testing, the unclear medical benefit of such testing, the format for disclosure of risk, and that the results will be placed in the EHR.

Individuals who agree to participate will undergo a blood draw for genotyping of the CHD susceptibility SNPs in a Central Laboratory Improvement Amendment (CLIA)-certified laboratory. Participants will return 6-10 weeks later (Visit 2) once genotyping is completed and a GRS calculated (Table 1). At this visit, patients will be allocated (1:1) to receive GRS vs. CRS alone and will undergo a 30-min CHD risk counseling session, followed by a visit with a physician for shared decision making regarding statin use. Three months following the disclosure of CHD risk, participants will return (Visit 3) for measurement of fasting lipid levels and assessment of changes in dietary fat intake and physical activity levels. The final study visit (Visit 4) will occur three months after Visit 3. Apart from incorporating the GRS into the CRS in one arm of the study, randomized patients will receive identical exposure to CHD risk education, assessment, and consideration for means of prevention. The study was approved by the Mayo Clinic IRB and is registered at ClinicalTrials.gov (NCT01936675).

**Table 1 Tab1:** Timeline for assessments

Measure	Visit 1	Visit 2	Visit 3	Visit 4
Body mass index				
Waist circumference				
Blood pressure				
Fasting lipid profile				
Fasting blood sugar				
Dietary fat intake				
Physical activity level				
Smoking status				

Visits 2, 3 and 4 occur approximately 2, 5 and 8 months after Visit 1,respectively

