### Disclosure of CHD risk

The CHD risk estimate will be disclosed by the genetic counselor during a 30-min semi-scripted session. Patients randomized to GRS will be shown a pictograph that incorporates the revised 10-year CHD risk based on the genotypes of the 28 CHD susceptibility SNPs. The control group will be shown a pictograph based on the CRS. The pictograph depicts 100 people “like the participant” and indicates how many in the next 10 years could be expected to experience an adverse CHD event and how many will not. The genetic counselor will help participants interpret and understand their results, highlighting the probabilistic nature of the genetic testing and that lifestyle factors such as diet, exercise, and smoking are major risk factors for developing CHD. The counselor will encourage participants to sign an action plan for behavioral change that includes increased physical activity and reduced dietary fat intake and smoking cessation if the participant is a smoker. Participants will be provided with a *Frequently Asked Questions* sheet that reiterates the key points conveyed by the genetic counselor at the visit.

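### Before-after change in diet, activity and psychosocial scores cannot be read as an effect of receiving CHD risk information, because both arms receive that information together with the same counselling

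*Protocol article*

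**What the plan says.** Three sections of the protocol article bear on this.

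- **Outcomes** says that dietary fat intake and physical activity "will be assessed at baseline and subsequent study visits to examine any changes over time as a result of receipt of CHD risk information".
- **Statistical methods**, after referring to the behavioural and psychosocial measures, says: "Within-participant analyses (using each participant as his/her own control) will be performed to evaluate changes in these measures over time". It continues: "Difference in scores will be examined for the outcomes by comparing post-results assessments to baseline assessments". The same section names the randomised arms as the primary groups. It plans t-tests for continuous outcomes, logistic regression comparing change by arm for binary outcomes, and regression-adjusted comparisons for both types. All secondary analyses are two-sided at 0.05.
- **Overall study design** and **Disclosure of CHD risk** describe what each arm receives. The first says: "Apart from incorporating the GRS into the CRS in one arm of the study, randomized patients will receive identical exposure to CHD risk education". The second says of the comparator: "The control group will be shown a pictograph based on the CRS". It also says, without restriction to one arm: "The counselor will encourage participants to sign an action plan for behavioral change that includes increased physical activity and reduced dietary fat intake".

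**The concern.** The aim in Outcomes is causal, and its cause is the receipt of CHD risk information. Using a participant as his or her own control makes the baseline value stand in for what would have happened without that information. This fails if anything else that moves the outcome happens between baseline and follow-up.

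Here something else does, by design. The counselling session that delivers the risk estimate also encourages a plan to raise physical activity and cut dietary fat, which are the two behaviours that Outcomes sets out to measure. No arm goes without the estimate or the counselling.

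The risk is that an improvement seen in both arms, or in one arm taken alone, is reported as an effect of disclosure. The opposite error is also possible. The Discussion raises the possibility that people at relatively low genetic risk become less motivated, and an improvement driven by counselling could hide this in a before-after analysis.

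**Working it through.** **1. What each contrast can identify.** Write the mean change from baseline in each arm as a sum of:
- r, the effect of receiving a CHD risk estimate;
- k, the effect of counselling, the action plan and the physician visit;
- t, the effect of time and repeat measurement;
- g, the effect of adding the GRS.

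Then:
- CRS arm: r + k + t
- GRS arm: r + k + t + g
- GRS minus CRS: g

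Two arm means identify two quantities, the sum (r + k + t) and g. No contrast in the design isolates r, yet r is what the wording in Outcomes asks for. The Background and the Discussion ask instead whether disclosure of genetic risk affects these outcomes. That question is about g, and the randomisation answers it.

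**2. Timing.** Baseline surveys are completed at Visit 1. Visits 2, 3 and 4 fall about 2, 5 and 8 months later, and disclosure takes place at Visit 2. A change to Visit 3 or Visit 4 thus spans about 5 or 8 months, of which about 2 precede disclosure. A psychosocial score taken at Visit 2 is only about 2 months from baseline.

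**3. The plan's own figure.** The detectable difference for the first LDL-C hypothesis is 25 × √(2/100) × 2.8 = 9.90 mg/dL, against the 9.9 stated. It reproduces, and nothing in this point alters it.

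**4. Illustration of size.** Inputs:
- n = 100 per arm, from an anticipated final sample of at least 200 allocated 1:1;
- two-sided 5% level, from Statistical methods;
- g = 0;
- a common shift d = r + k + t, in SDs of the change score. The documents give no value, so d is an assumption shown over a range.

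The before-after rejection probability (normal approximation) is Φ(d√n − 1.96) + Φ(−d√n − 1.96). For d = 0.2 and n = 100, d√n = 2.0, so Φ(0.04) + Φ(−3.96) = 0.52. The probability that exactly one arm is significant is 2p(1 − p), where p is the one-arm value.

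| Assumed d (SD of change) | One arm, n = 100 | Pooled, n = 200 | One arm significant, the other not | Between-arm test |
|---|---|---|---|---|
| 0.1 | 0.17 | 0.29 | 0.28 | 0.05 |
| 0.2 | 0.52 | 0.81 | 0.50 | 0.05 |
| 0.3 | 0.85 | 0.99 | 0.25 | 0.05 |
| 0.5 | >0.99 | >0.99 | <0.01 | 0.05 |

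The fourth column matters if the arms are tested separately and the results set side by side. With no GRS effect and a shift of 0.2 SD, the two arms would disagree on significance about half the time.

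**5. The reverse error.** If d = 0.3 and the GRS reduced motivation by 0.1 SD, the GRS arm would still show a before-after gain of 0.3 − 0.1 = 0.2 SD.

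**The case against.** The strongest reply is that the plan never says the attribution rests on before-after analysis. The sentence on within-participant analyses gives its own aim as evaluating change over time, which is descriptive. The causal phrase is in another section and names no analysis. Statistical methods already makes the randomised arms the primary groups and plans between-arm comparisons for binary and continuous outcomes. The score difference it describes may simply be the change score used in those comparisons. On this view, a before-after test that rejects when the mean has truly shifted by 0.3 SD is answering its stated question correctly.

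Much of this stands, and it rules out several stronger readings that a reader might infer:

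- *That no randomised comparison of these measures is planned.* It is planned. What is not stated is adjustment for the baseline score in continuous outcomes. An article may leave that detail to the analysis plan, so its absence is not a defect on its own.
- *That psychosocial change is also explicitly attributed to receipt of risk information.* The causal phrase covers diet and activity only. Several psychosocial items, such as satisfaction with counselling, have no meaningful baseline.
- *That every participant signs an action plan.* Signing is only encouraged.
- *That all comparisons span 5 to 8 months.* This holds for Visits 3 and 4, not for a score taken at Visit 2.
- *That season and regression to the mean bias the results.* Enrolment dates are not given, and eligibility does not select on diet, activity or psychosocial scores. Neither mechanism is established.
- *That 85% is the plan's false-positive rate.* It depends on an assumed shift, and it is an error rate only if the before-after result is read as a disclosure effect.

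The between-arm analyses still do not rescue the aim as worded in Outcomes. They estimate g, whereas that wording asks about r. The only planned analysis that appears to address r is the own-control one, and it cannot separate r from the counselling. Statistical methods also does not label the own-control analyses descriptive.

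**Conclusion.** The concern holds in a limited form. Outcomes states a causal aim that no contrast in this design can meet, and the own-control analyses cannot supply the missing attribution because both arms receive risk information and the same lifestyle counselling. The randomised comparison identifies the effect of adding the GRS and nothing wider.

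The conclusion rests on the described content of the two arms, not on the illustration. The rejection rates (0.17 to above 0.99 in one arm for shifts of 0.1 to 0.5 SD) show only how readily a common shift would reach significance, and the size of that shift is assumed.

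The consequence is confined to the interpretation of secondary behavioural and psychosocial outcomes. Both formal hypotheses, the primary outcome and the power calculation concern LDL-C and do not change. The correction is worth making because it governs what may be concluded.

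**What to change.** - **Statistical methods:** state that the inferential analysis for dietary fat intake, physical activity and each psychosocial measure with a baseline is the GRS-versus-CRS difference, adjusted for the baseline score. Label within-participant changes descriptive, and report them by arm without a claim of effect.
- **Outcomes:** replace the aim of examining change resulting from receipt of CHD risk information with the effect of adding the GRS to CHD risk information. This agrees with the Background and the Discussion.

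The cost is wording and one model specification, using data already planned for collection. The price is that changes within an arm can no longer be claimed as effects of disclosure.

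### Comparing the change in a yes/no outcome by logistic regression is ill-defined and, on two natural readings, usually less efficient than comparing post-disclosure status

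*Protocol article*

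**What the plan says.** The protocol article, Statistical methods, states: "Logistic regression will be used for binary outcomes (e.g., % achieve accurate understanding of their CHD risk) to compare the change by arm". The result is to be given as odds ratios with 95% confidence intervals.

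The two sentences before it describe comparisons with baseline: "Within-participant analyses (using each participant as his/her own control) will be performed to evaluate changes in these measures over time" and "Difference in scores will be examined for the outcomes by comparing post-results assessments to baseline assessments". The sentence after it reads "Adjusted comparisons of binary and continuous outcomes will be performed using regression models" and names no covariates. Earlier in the section, frequencies of categorical factors "will be compared using either the Chi-Square or Fisher’s exact test". On the error rate: "All secondary analyses will be based on two-sided tests at a significance level of 0.05".

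The Abstract places the psychosocial measures at baseline and after disclosure. Sample size and power gives figures for LDL-C only. The article states no rate, effect size or within-person correlation for any binary outcome.

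**The concern.** Between two visits a participant can gain accuracy, lose it, or stay the same. That is three states, and ordinary logistic regression needs a response with two. An analyst who takes the word *change* literally has two natural routes:

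- **Arm-by-time contrast.** The arms are compared on the shift in log odds from baseline to follow-up. The result is a ratio of odds ratios, and it carries the sampling noise of the baseline odds. Randomisation already makes the arms comparable at baseline in expectation, so subtracting the baseline helps only if it is strongly correlated with follow-up.
- **Became-accurate indicator.** Success means inaccurate before and accurate after. People accurate at both times are then grouped with those who never became accurate, which pulls the odds ratio towards 1.

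At stake are the precision and the meaning of the reported odds ratio for understanding of CHD risk. This is the article's own example of a binary outcome, and comprehension and perception of risk come first in its section on psychosocial measures.

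**Working it through.** **1. The plan's own figure.** The only power statement concerns LDL-C ("with 80 % power and 5 % Type I error rate"). With SD 25 mg/dL and 100 per arm, 25 × sqrt(2/100) × 2.8 = 9.9 mg/dL, as stated. Nothing comparable exists for a binary outcome, so I take over the 100 per arm and two-sided 0.05, and assume the rest.

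**2. Assumptions.** Baseline accuracy 10%, 30% or 50% in both arms; follow-up accuracy 40 v 60% or 50 v 70%; within-person correlation phi from 0 to 0.7, wherever phi is mathematically possible with those rates.

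**3. Formulas** (n = 100 per arm).

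- v(p) = 1/[n p(1−p)], the variance of a log odds.
- Post-disclosure status: d = logit(p1) − logit(p0); SE² = v(p0) + v(p1).
- Arm-by-time, allowing for the pairing: same d; SE² = sum over arms of v(b) + v(p) − 2c, where b is baseline accuracy and c = phi / [n sqrt(b(1−b)p(1−p))].
- Became accurate: q = p − [bp + phi sqrt(b(1−b)p(1−p))] in each arm; d = logit(q1) − logit(q0); SE² = v(q0) + v(q1).
- Power = Φ(d/SE − 1.96).

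**4. One setting in full:** baseline 30%, follow-up 40 v 60%, phi 0.2.

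- Post-disclosure status: d = 0.811; SE = sqrt(0.0417 + 0.0417) = 0.289; power = Φ(2.81 − 1.96) = 0.80.
- Arm-by-time: v(b) = 0.0476 and c = 0.0089. Each arm contributes 0.0476 + 0.0417 − 0.0178 = 0.0715. SE = sqrt(0.1429) = 0.378; power = Φ(2.14 − 1.96) = 0.57.
- Became accurate: q0 = 0.235 and q1 = 0.375. d falls to 0.669; SE = sqrt(0.0556 + 0.0427) = 0.313; power = Φ(2.14 − 1.96) = 0.57.

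**5. All settings.** The last column is simulated, with 400 trials per setting (Monte Carlo SE near 0.8 is sqrt(0.8 × 0.2/400) = 0.02).

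| Baseline accuracy | Post status, unadjusted | Arm-by-time, phi 0-0.3 | Arm-by-time, phi 0.5-0.7 | Became accurate | Post status, baseline-adjusted |
|---|---|---|---|---|---|
| 10% | 0.80-0.82 | 0.31-0.39 (phi 0 and 0.2 only) | not possible | 0.72-0.73 | 0.81-0.85 |
| 30% | 0.80-0.82 | 0.48-0.66 | 0.77 (phi 0.5; 40 v 60% only) | 0.52-0.63 | 0.81-0.91 |
| 50% | 0.80-0.82 | 0.52-0.70 | 0.81-0.83 (phi 0.5); 0.96 (phi 0.7; 40 v 60% only) | 0.34-0.67 | 0.81-0.98 |

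**6. When the arm-by-time loss disappears.** It does so once 2c ≥ v(b), that is phi ≥ 0.5 × sqrt[p(1−p) / (b(1−b))]. For follow-up 40 v 60%:

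- At 50% baseline the threshold is 0.5 × sqrt(0.24/0.25) = 0.49, which is attainable.
- At 10% baseline it is 0.5 × sqrt(0.24/0.09) = 0.82. The largest phi possible with 10% and 60% is sqrt[(0.1 × 0.4)/(0.6 × 0.9)] = 0.27, so the loss cannot disappear.

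**The case against.** The strongest reply is that the sentence need not mean either problematic analysis. Its example speaks of the percentage who *achieve* accurate understanding, which fits status after disclosure, and it promises odds ratios, not ratios of odds ratios. On that reading there is no loss of power. The next sentence allows adjusted regression for binary outcomes, so a baseline-adjusted model is already within the plan. A condensed article may also leave the exact model to the SAP. All of this stands, and it makes the point minor. It does not remove it: the contrast is stated here as a change, directly after two sentences on comparison with baseline, and if post-disclosure status was meant then the word is wrong.

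A reader might infer more than the article supports:

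- **That most of the power is lost.** Arm-by-time loses more than half only at 10% baseline accuracy among the settings tried, and the became-accurate indicator only at 50% baseline with low correlation. Elsewhere the loss is partial or absent. The two losses also peak at opposite ends of the baseline range, so both cannot be large together.
- **That repeated records will be treated as independent.** The article nowhere says that baseline and follow-up records will be stacked, and it speaks of each participant as their own control.
- **That baseline accuracy means something different in each arm.** One arm sees a genotype-informed risk, while "The control group will be shown a pictograph based on the CRS". But the article does not define accurate understanding as matching the number shown, nor say how baseline answers are scored.
- **That the randomised comparison is biased.** Nothing stated implies this. The issue is efficiency and what the estimate means.

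**Conclusion.** The point holds as a minor one. The stated contrast suits a yes/no outcome badly. Followed as an arm-by-time term or a became-accurate indicator, it is usually less efficient than post-disclosure status adjusted for baseline, and it was not more powerful in any setting tried. The exception to a material loss is arm-by-time at correlation of about 0.5 or more, which needs baseline accuracy well above 10%.

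The power figures rest on assumed accuracy rates and correlations, because the article gives none; only the 100 per arm and the 0.05 level come from it. The outcome is secondary and psychosocial. The LDL-C primary comparison and its sample size are untouched.

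**What to change.** Replace the reference to change by arm with wording such as: *Binary outcomes will be analysed by logistic regression of post-disclosure status on randomised arm, adjusted for the baseline response where it was measured and for the factors balanced at randomisation (age, sex, family history of CHD); the arm odds ratio will be reported with its 95% confidence interval.* For outcomes with no baseline measurement, the baseline term is dropped.

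The within-participant summaries can stay as description of change over time. The cost is one sentence. No new data are needed, since psychosocial measures are already planned at baseline and after disclosure and the randomisation factors are known for everyone randomised.
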